## Abstract

**Background:**

Intermittent preventive treatment in pregnancy (IPTp) with sulfadoxine-pyrimethamine (SP) is recommended by the World Health Organization for the prevention of malaria in pregnancy (MIP)-associated adverse outcomes in high burden areas. However, the efficacy of IPTp-SP has decreased in step with increasing parasite drug resistance. Suitable alternative strategies are needed.

**Methods:**

This is a protocol for a phase IIIb open-label, two-armed randomized controlled superiority trial to assess the safety and efficacy of a hybrid approach to IPTp combining screening and treatment with dihydroartemisinin-piperaquine (DP) to the current IPTp-SP regimen at the first antenatal care clinic visit. Pregnant women without HIV infection and without signs or symptoms of malaria will be randomized to either standard IPTp-SP or hybrid IPTp-SP plus screening and treatment (IPTp-SP+). In the IPTp-SP+ arm, participants who screen positive by rapid diagnostic test for *P. falciparum* will be treated with DP at the first antenatal visit while those who screen negative will receive SP per current guidelines. All participants will be administered SP on days 35 and 63 and will be actively followed biweekly up to day 63 and then monthly until delivery. Infants will be followed until 1 year after delivery. The primary endpoint is incident PCR-confirmed MIP at day 42. Secondary endpoints include incident MIP at other time points, placental malaria, congenital malaria, hemoglobin trends, birth outcomes, and incidence of adverse events in infants up to the first birthday.

**Discussion:**

A hybrid approach to IPTp that combines screening and treatment with an artemisinin-based combination therapy at the first visit with standard IPTp-SP is hypothesized to confer added benefit over IPTp-SP alone in a high malaria transmission area with prevalent SP resistant parasites.

**Trial registration:**

Pan African Clinical Trials Registry 201905721140808. Registered retrospectively on 11 May 2019

**Supplementary Information:**

The online version contains supplementary material available at 10.1186/s13063-021-05745-0.

## Administrative information

Numbers in curly brackets refer to SPIRIT checklist items. The order of the items has been modified to group similar items (see http://www.equator-network.org/reporting-guidelines/spirit-2013-statement-defining-standard-protocol-itemsfor-clinical-trials/). The SPIRIT figure is included as an additional file and the World Health Organization (WHO) Trial Registration Data Set is attached as annex (see supplementary table).

## Background and rationale {6a} {6b}

Malaria poses a major public health risk to pregnant women residing in areas of high *Plasmodium falciparum* transmission [1]. Pregnant women face greater risk of infection and infection-related complications compared to other adults [2]. In high burden areas, malaria in pregnancy (MIP) is usually asymptomatic and is linked to a variety of adverse outcomes including maternal anemia, maternal and perinatal mortality, congenital infection, fetal growth restriction, low birth weight, pre-term birth, and miscarriage [2–5]. The World Health Organization (WHO) therefore recommends intermittent preventive treatment in pregnancy (IPTp) with sulfadoxine-pyrimethamine (SP) to reduce MIP and associated complications in high malaria transmission areas [6].

IPTp relies on contact with patients during scheduled antenatal care clinic (ANC) visits at 4- to 6-week intervals. Treatment doses of antimalarial medication are presumptively administered without prior malaria laboratory testing to clear any potential existing infection and, for a limited post-treatment duration, to protect against subsequent infection [6]. IPTp-SP has been essential in reducing MIP-associated adverse outcomes, with the greatest impact seen when at least three doses of SP are administered throughout a pregnancy [7, 8]. However, the efficacy of SP is waning due to expanding drug resistance [9].

Resistance to SP is caused by point mutations in the genes encoding dihydropteroate synthase (*dhps*) and dihydrofolate reductase (*dhfr*) [10]. Recent studies show that in areas with high prevalence of *dhps* K540E quintuple mutations IPTp-SP effectiveness is reduced but remains associated with increases in birth weight and maternal hemoglobin compared to no IPTp-SP [11, 12]. However, studies from Tanzania and Malawi found that *dhps* A581G sextuple mutations are associated with a greater risk of low birth weight and high peripheral parasitemia, and increased placental infection and inflammation [9, 13]. In Zambia, evidence points to increasing SP resistance and a corresponding increase in breakthrough parasitemia [14, 15]. The prevalences of quintuple and sextuple mutations were estimated to be 17–61% and 2–3%, respectively, in our northern Zambia study site, and were associated with SP failures of 26% and 22% [14, 15].

At present, WHO continues to recommend IPTp-SP in malarious regions where SP resistance remains below certain thresholds while alternative strategies are under investigation [6, 16]. This clinical trial protocol tests the safety and efficacy of a hybrid approach that combines screening and treatment with rapid diagnostic test (RDT) and dihydroartemisinin-piperaquine (DP) at the first antenatal visit in addition to standard IPTp-SP to reduce the incidence of MIP and improve maternal and birth outcomes in a high-transmission area with moderate to high prevalence of *dhps* K540E quintuple mutations.

### Trial objectives {7} {12}

This research protocol is designed to assess the safety and efficacy of a revised IPTp schedule that incorporates a screen-and-treat strategy using RDT and DP at the first antenatal care visit (IPTp-SP+). The research objectives and corresponding endpoints are listed in Table 1.

**Table 1 Tab1:** Outcomes

Objectives	Outcomes/endpoints
Primary objectives	
To compare the effectiveness of IPTp-SP versus IPTp-SP+ for treating and preventing maternal *P. falciparum* infection To compare the safety and tolerability of IPTp-SP versus IPTp-SP+	• Relative hazard of *P. falciparum* infection diagnosed by PCR at day 42 after randomization (primary outcome) • Relative hazard of *P. falciparum* infection diagnosed by PCR or microscopy at days 14, 28, 35, 42, 63, delivery, and 1-month post-partum in infants • Proportion who experience at least one episode of *P. falciparum* infection by day 14, 28, 35, 42, or 63 • Proportion with treatment or prevention failure at day 42 stratified according to study drug (SP or DP) • Median time to first episode of MIP • Acute, chronic, and prior placental infection at delivery • Medication-related adverse events and serious adverse events until 1-year post-partum (primary outcome)
Secondary objectives	
To compare the effectiveness of IPTp-SP versus IPTp-SP+ for reducing complications of MIP	• Mean birth weight and prevalence of low birth weight (within 72 hours post-partum), neonatal mortality (within 28 days post-partum), congenital malaria diagnosed by PCR, placental malaria diagnosed by histopathology using placental biopsies, maternal anemia (hemoglobin changes at days 14, 28, 42 and 63), congenital anemia, Incidences of pregnancy losses, congenital *P. falciparum* infection
To compare selection for drug resistant parasites between infected individuals in the IPTp-SP and IPTp-SP+ treatment groups	• Relative allele frequencies of genotypic markers of drug resistance in malaria parasites
To measure piperaquine exposure and duration	• Terminal elimination half-life of piperaquine determined by noncompartmental analysis of drug concentrations at 0, 14, 28, 35 and 42 days

*MIP* malaria in pregnancy, *PCR* polymerase chain reaction, *IPTp-SP* intermittent prevent treatment in pregnancy with sulfadoxine-pyrimethamine; *IPTp-SP+*, intermittent prevent treatment in pregnancy with sulfadoxine-pyrimethamine plus screen-and-treat with dihydroartemisinin-piperaquine at first occasion; *SP*, sulfadoxine-pyrimethamine

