### Clinical procedures {11d} {13} {15} {26a}

Study procedures are outlined in Table 3 and the flow of events is shown in Fig. 1. The informed consent will be administered by a study nurse in the local language (Bemba) and/or in English as preferred by the participant. Assent will be obtained from participants <18 years old, and informed consent will be obtained from those ≥18 or the legally authorized representative for minors. If the participant cannot provide a written signature, then a thumbprint will be obtained. After collection of demographic data, provision of informed consent, baseline medical and obstetric history, and physical examination by a study physician including eligibility assessment, participants will be randomized to either the IPTp-SP or IPTp-SP+ treatment groups. All participants will undergo hemoglobin measurement as part of the screening process. On enrollment, fingerstick blood will be drawn for preparation of dried blood spots (DBS) for subsequent molecular testing. In addition, participants randomized to the experimental group (IPTp-SP+) will undergo RDT.

**Table 3 Tab3:** Schedule of events

	Antenatal period *Study day*									Postpartum period *Study month*			
Event	0	1–2	14	28	35	42	63^a^	Unsch.	Birth	1	6	9	12
Informed consent/oral assent	•												
Medical history	•												
Physical examination, including height, weight, temperature	•		•	•	•	•	•	•	•				
Fetal viability	•		•	•	•	•	•	•	•				
Focused history and examination			•	•	•	•	•	•	•	•	•	•	•
Adverse event evaluation	•	•	•	•	•	•	•	•					
IPTp-SP^b^	•				•		•						
RDT^c^	•												
Treatment with DP^d^	•	•											
DBS for PCR, genotyping	•		•	•	•	•	•	•	•				
Malaria microscopy^e^			•	•	•	•	•	•	•				
Hemoglobin measurement	•		•	•		•	•		•	•			
Blood sample for PK^d^	•		•	•	•	•							
Delivery									•				
Placental biopsy, cord blood									•				
Infant assessment including history and exam, weight, heel stick									•	•	•	•	•

^a^Monthly visits continue until delivery

^b^Includes participants randomized to standard IPTp-SP, participants randomized to IPTp-SP+ who test negative at the first visit, and all participants in both groups at days 35, 63 and then monthly until delivery

^c^Limited to participants randomized to IPTp-SP+

^d^Limited to participants randomized to IPTp-SP+ who test positive by RDT at the first visit

^e^Only participants with signs or symptoms of malaria will undergo microscopy

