**Fig. 1 Fig1:**
[figure not shown]
Study flow diagram. *ANC*, antenatal care. *DP*, dihydroartemisinin-piperaquine. *IPTp-SP,* intermittent preventive treatment in pregnancy with sulfadoxine-pyrimethamine with (+) or without screen-and-treat. *RDT*, rapid diagnostic test for *P. falciparum* infection

Treatment with either SP or DP will be administered as described above. Participants will return for follow-up on days 14, 28, 35, 42, and 63 and then monthly thereafter until delivery. They will be instructed to report to the clinic for any illness between scheduled visits.

At each scheduled or unscheduled visit, the study clinician will perform an interval history and physical examination, including an updated medication history. During the active follow-up period (up to day 63), DBS will be collected and hemoglobin will be measured. SP will be given on days 35 and 63. Additional doses of SP will be given during monthly visits until delivery with a minimum of 4 weeks between doses and laboratory samples (e.g., blood slide for microscopy, urinary tests, full blood count) will be collected if clinically indicated according to signs and symptoms. Antimalarials or antibiotics with antimalarial activity (e.g., systemic erythromycin, macrolide antibiotics, trimethoprim-sulfamethoxazole or other sulphonamides, tetracyclines, quinolones, clindamycin) will be prohibited during the active follow-up period.

Participants who present during the follow-up period with any signs or symptoms of malaria will undergo testing by thick smear, and DBS will be collected from those with positive microscopy. The signs and symptoms that we will consider indicative of possible clinical malaria include fever, chills, weakness, fatigue, myalgia, arthralgia, headache, anorexia, nausea, vomiting, abdominal pain, or diarrhea. All confirmed uncomplicated malaria cases will be treated with artemether-lumefantrine according to national guidelines (Coartem™ 20 mg/120 mg four tablets taken at 0, 8, 24, 36, 48, and 60 h). Participants who develop severe malaria defined according to WHO criteria will be referred to SPGH for inpatient management [20].

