On the day of delivery, the participant and infant will be evaluated as soon as possible after delivery. The birthweight will be measured, and an assessment for congenital abnormalities will be done. Obstetric complications including but not limited to hemorrhage, premature rupture of membranes, cesarean section, and others will be captured as adverse events. Congenital abnormalities, if present, will also be recorded. Thick and thin peripheral blood films, DBS, and hemoglobin measurement will be done on both the participant and infant. In addition, cord blood, placental blood films for thick and thin smear microscopy, placental DBS, and placental biopsy for histopathological analysis will be collected.

Infants will be reassessed at 1, 6, 9, and 12 months postpartum for focused history and physical examination, including interval medication and hospitalization history, growth, and assessment of developmental milestones. At the first monthly visit, hemoglobin measurement and malaria parasitology by thick smear and PCR testing using DBS prepared from heel stick blood will be performed.

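### The PCR sampling rule for symptomatic women contradicts the visit schedule and could leave slide-negative women without the test that defines the primary endpoint

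*Protocol article*

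**What the plan says.** All references are to the protocol article.

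- **Endpoints (Table 1).** The primary outcome is the relative hazard of *P. falciparum* infection by PCR at day 42. A further outcome is the relative hazard of "infection diagnosed by PCR or microscopy at days 14, 28, 35, 42, 63, delivery, and 1-month post-partum in infants".
- **PCR schedule (Table 3).** The row "DBS for PCR, genotyping" is marked at days 0, 14, 28, 35, 42 and 63, at unscheduled visits and at birth. No footnote limits it.
- **PCR in the text, unconditional (Clinical procedures, after Fig. 1).** In the paragraph on scheduled and unscheduled visits: "During the active follow-up period (up to day 63), DBS will be collected and hemoglobin will be measured".
- **PCR in the text, conditional (same section, next paragraph).** Women who present with any sign or symptom of malaria "will undergo testing by thick smear, and DBS will be collected from those with positive microscopy".
- **Microscopy (Table 3, footnote e).** "Only participants with signs or symptoms of malaria will undergo microscopy". The row carrying this footnote is marked at days 14 to 63, at unscheduled visits and at birth.
- **Delivery (Clinical procedures).** "Thick and thin peripheral blood films, DBS, and hemoglobin measurement will be done on both the participant and infant". The text attaches no symptom condition. All infants also get a thick smear and PCR at the first monthly visit.

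**The concern.** Two pairs of instructions cannot both be followed.

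The first pair matters more. Table 3 and one sentence of the text give every woman a DBS. Another sentence makes the DBS of a symptomatic woman depend on a positive slide. The slide would then decide who receives the test that defines the primary endpoint. A symptomatic woman with a negative slide would have no PCR result at that visit. If the blank is read as negative, an infection too sparse for the slide counts as no infection.

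The rule is not confined to rare sick visits. It applies during follow-up without exempting scheduled visits, and its triggers include fatigue, headache, nausea and abdominal pain, which are common in pregnancy. Enrolment is more lenient: a woman counts as asymptomatic with fewer than three of five listed symptoms (Table 2, footnote b). During follow-up, any one sign or symptom triggers the smear.

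The second pair concerns delivery. Footnote e restricts the birth slide to symptomatic women, and the delivery paragraph films all of them.

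A reporting trap follows. From day 14 to day 63 slides exist only for women with symptoms, so a hazard based on slides alone would describe symptomatic parasitaemia in women who reported symptoms in an open-label trial. It would not describe infection.

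**Working it through.** **Step 1. The rules side by side**

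| Place | Who has a DBS for PCR | Who has a slide |
|---|---|---|
| Table 3 | All, at days 0–63, unscheduled visits and birth | Symptomatic women only (footnote e), days 14–63, unscheduled visits and birth |
| Clinical procedures, routine visits | All, up to day 63 | – |
| Clinical procedures, symptomatic women | Those with a positive slide | All with signs or symptoms |
| Clinical procedures, delivery | All mothers and infants | All mothers and infants |
| Clinical procedures, infants at month 1 | All infants | All infants |

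Rows 1 and 2 disagree with row 3 on the DBS. Row 1 disagrees with row 4 on the birth slide.

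**Step 2. What the conditional rule does if followed**

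- At day 42, a woman with a headache and a negative slide has no PCR result at the primary time point.
- At day 35, the same woman has no DBS and then receives the scheduled SP dose. If that clears the infection, day 42 is negative and the event is lost.
- At an unscheduled visit, an infection that the slide misses is lost if it is gone by the next scheduled DBS.

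The slide has a floor that follows from the laboratory section. It is called negative after 2000 leukocytes, with 8000 leukocytes per µL assumed. One parasite in that count corresponds to 8000 / 2000 = 4 parasites per µL. The detection limit of the PCR is not given.

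**Step 3. The plan's own sample size**

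Inputs: 22–26% PCR prevalence, a 50% reduction, two-sided alpha 0.05, 80% power, 162 per arm (Sample size calculation). I take the midpoint: p₁ = 0.24, p₂ = 0.12, p̄ = 0.18.

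n = [1.96·√(2p̄(1−p̄)) + 0.842·√(p₁(1−p₁) + p₂(1−p₂))]² / (p₁−p₂)²
= [1.96·0.543 + 0.842·0.537]² / 0.0144 ≈ 160 per arm.

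This is close to the stated 162. Power at 162 per arm is 80.6%.

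**Step 4. Illustration of the loss**

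Let s be the share of infected women who are symptomatic at the visit, and m the sensitivity of microscopy relative to PCR. Neither is in the documents, so the ranges are assumptions: s from 5% to 30%, m from 30% to 70%.

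Share of PCR-positive infections missed: L = s(1−m). Detected proportions become p₁(1−L) and p₂(1−L).

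| s | m | L | p₁, p₂ detected | Power, 162 per arm |
|---|---|---|---|---|
| 0.05 | 0.70 | 0.015 | 0.236, 0.118 | 79.8% |
| 0.10 | 0.50 | 0.050 | 0.228, 0.114 | 78.1% |
| 0.20 | 0.50 | 0.100 | 0.216, 0.108 | 75.3% |
| 0.30 | 0.30 | 0.210 | 0.190, 0.095 | 68.7% |

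Within these assumptions the figures are upper-end, because some missed infections would be found at the next scheduled DBS.

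**Step 5. Power or bias?**

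The observed ratio of detected proportions is the true ratio × (1−L₊)/(1−L₀), where L₊ and L₀ are the losses in the IPTp-SP+ and IPTp-SP arms. With equal losses the ratio stays at 0.50 and the cost is power alone. With unequal losses it shifts. The extremes of the assumed range give 0.50 × 0.79/0.985 = 0.40 and 0.50 × 0.985/0.79 = 0.62. These are outer bounds, not expectations. The documents do not show which direction would apply.

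**The case against.** The strongest reply is that Table 1 says PCR *or* microscopy, and PCR is scheduled at every listed maternal visit and for infants at delivery and at 1 month. An asymptomatic woman without a slide is then classified by her PCR. This stands. A reader might infer that the endpoint cannot be measured as written. The documents do not support that, because Table 1 does not promise both tests at each visit.

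Second, the conditional sentence does not say that DBS is taken *only* after a positive slide. It could describe an extra sample at illness visits, including those after day 63. That reading is possible and would protect the scheduled days 35 and 42. It still leaves a conflict with Table 3, which marks DBS at unscheduled visits without restriction. Nothing in the text tells site staff which reading applies.

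Third, the size rests on assumed figures, and the low end leaves power at about 80%. This also stands: the illustration shows what could happen and does not estimate what did.

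Fourth, a reader might conclude that clinical malaria must be added as an endpoint because the trial detects and treats it. Choosing infection over clinical malaria contradicts nothing in the protocol, which itself describes malaria in pregnancy as usually without symptoms. Nor do the documents support redefining every infection endpoint as PCR only: at delivery and at the infant 1-month visit the text provides slides for all, and those results are usable.

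**Conclusion.** The point holds as two contradictions in the current text. The DBS rule for symptomatic women conflicts with Table 3 and with the unconditional sentence in the same section. Footnote e at birth conflicts with the delivery paragraph.

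The first can reach the primary endpoint, but only if sites followed the conditional rule and the resulting blanks were treated as negative. Its size is unknown. It depends on the symptomatic share of infected women and on microscopy sensitivity, neither of which is given. If the losses are equal in both arms the cost is power. Bias requires unequal losses, which open-label symptom reporting makes possible but which nothing in the protocol demonstrates.

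The second is a matter of wording. The endpoint in Table 1 remains measurable through scheduled PCR. The one limit on its microscopy component is that slides from days 14 to 63 cannot support a stand-alone infection hazard.

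**What to change.** 1. Amend the sentence on symptomatic women so that DBS is taken at every scheduled and unscheduled visit marked in Table 3, whatever the slide result.
2. State which rule the sites followed. Where a DBS was withheld after a negative slide, code the visit as PCR not done, not PCR negative. It then enters the interval-censoring and multiple-imputation methods already named under Statistical analysis. Symptoms and slide result belong in the imputation model, because they determine which results are missing. Report the number of such visits by arm.
3. Exempt birth from footnote e, in line with the delivery paragraph.
4. Do not report a microscopy-only hazard for days 14 to 63 as infection. Keep the slide results at delivery and at the infant 1-month visit.

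**Cost.** A few sentences, some recoding, and a few more PCR assays where cards exist. Recruitment ended on 19 June 2020, so the last day 63 visit fell around 21 August 2020. A DBS not collected by then cannot be recovered, and for those visits only the coding can be put right.

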#### Primary objectives

The two primary objectives are to compare the effectiveness of IPTp-SP with or without screen-and-treat with DP at first antenatal care contact in treating and preventing MIP and to describe the safety profiles of IPTp-SP and IPTp-SP+ including incidence of maternal and perinatal/infant adverse events until 1 year post-partum.

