### Intervention {11a} {11b} {11c}

The intervention will consist of IPTp-SP with or without screen-and-treat using DP at the first ANC visit. Participants randomized to the IPTp-SP+ group who test positive by rapid diagnostic test (RDT) will be given a full treatment course of DP (D-ARTEPP® 40 mg/320 mg three tablets daily for 3 days; Guilin Pharmaceutical) under direct observation (DOT) by a study nurse (day 0) or community health worker (days 1–2). All other participants will be treated with SP at the first visit, including those in the IPTp-SP+ arm with a negative RDT result, and all participants in both groups will be given SP at all subsequent visits (day 35, day 63, then monthly until delivery) under DOT. IPTp-SP will be administered according to national guidelines (G-SCOPE® 1,500 mg sulfadoxine/75 mg pyrimethamine for one dose no fewer than 4 weeks between doses; Guilin Pharmaceutical). Participants will be observed for 1 h post-dose to monitor for vomiting or other adverse reactions. If vomiting occurs within 30 min, the full dose will be readministered. If vomiting occurs after 30 min, half of the total dose will be readministered. In the case of persistent vomiting, the participant will be withdrawn from the study and referred for alternative treatment.

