#### Plasma piperaquine concentrations

Participants who are randomized to the IPTp-SP+ who screen positive and are administered DP treatment will have an additional 2 mL blood collection for measurement of piperaquine plasma concentrations on days 0, 14, 28, 35, and 42. Piperaquine quantitation will be done using liquid chromatography tandem mass spectrometry as previously described [25]. The terminal elimination half-life will be estimated using noncompartmental analysis, and the effect of age, body surface area, body mass index, and gestational age on drug concentrations will be explored in mixed effects models using WinNonlin software (Certara, Princeton, NJ).

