### Statistical analysis {20a} {20b} {20c}

Longitudinal data will be displayed using the nonparametric Kaplan-Meier estimations of the survival function. The primary analysis will be comparison of the 42-day incidence of MIP using multivariate models to estimate the relative hazard between the IPTp-SP and IPTp-SP+ groups according to intention-to-treat (ITT). Testing for proportionality of hazards will be done using formal statistical testing with Schoenfeld residuals as well as visual inspection of the nonparametric survival estimates. For non-proportional hazards, an extended Cox model will be applied. To handle interval censoring due to participants who miss one or more follow-up visits, we will use parametric models for interval-censored survival-time data. The relative hazard will be estimated in parametric models accounting for recurrent events by using a robust variance estimator. For the primary safety analysis, we will compare the proportions of serious and non-serious AEs using logistic regression models and relative hazards of AEs using Cox regression methods as above. Secondary analyses of continuous outcomes (hemoglobin concentration, birthweight) will be examined in linear regression models and in logistic regression models for binary outcomes (prevalence of low birth weight, neonatal mortality, placental malaria, congenital malaria, maternal anemia, congenital anemia, drug resistance allele frequency). Prespecified subgroup analyses will be done according to the following strata: primigravidae, multigravidae, gestational age at enrollment, delivery before or after the day 63 visit, treatment dose on a mg/kg basis, positive *P. falciparum* PCR on enrollment, and presence or absence of quintuple and sextuple mutations. In a secondary analysis, we will compare the proportions of treatment failures and prevention failures according to the antimalarial drug given at the first encounter (SP or DP) in an on-treatment analysis using logistic regression. Treatment failures will be defined as recurrent infections that are determined by genotyping to be recrudescent parasites from the initial infection in participants who tested positive by PCR at the initial visit. Prevention failures will be defined as PCR-confirmed parasitemia in participants who initially tested negative by PCR at the first visit, or who tested positive by PCR at the first visit but who experienced reinfection with a new parasite as determined by genotyping. No interim analysis is planned. Every effort will be made to collect complete data for all participants and minimize missing data. Missing data will be handled using multiple imputation.

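### The primary safety comparison runs to 1 year post-partum with no window before day 35, although study drug differs by arm only at the first visit, so later shared SP doses dilute any acute tolerability difference

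*Protocol article*

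**What the plan says.** Table 1 (Trial objectives) lists a primary safety outcome: "Medication-related adverse events and serious adverse events until 1-year post-partum (primary outcome"). The Primary objectives section repeats the horizon and extends it to the child, "including incidence of maternal and perinatal/infant adverse events until 1 year post-partum".

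The Intervention section limits the difference in study drug to the first visit. RDT-positive women in the IPTp-SP+ arm receive DP over days 0-2. For the rest, "All other participants will be treated with SP at the first visit, including those in the IPTp-SP+ arm with a negative RDT result". After that, "all participants in both groups will be given SP at all subsequent visits (day 35, day 63, then monthly until delivery) under DOT". Footnote b of Table 3 says the same.

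For the primary safety analysis, the Statistical analysis section states: "we will compare the proportions of serious and non-serious AEs using logistic regression models and relative hazards of AEs using Cox regression methods", the Cox methods being those already described for efficacy. It gives no time window for AEs. The analysis by drug received at the first encounter covers treatment and prevention failures only, and none of the listed subgroups is an AE period.

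**The concern.** What is new in the experimental arm is one course of DP in place of one dose of SP, in some of the women. An acute tolerability difference caused by that swap would appear mainly before the day-35 dose. After that, both arms face the same SP doses. A woman counted once for any medication-related AE over the whole period can qualify through any of those later doses, so the two cumulative proportions move closer together.

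At stake is how a null safety result would be read. A finding of no difference in AEs could owe much to both arms having taken the same drug for the rest of pregnancy. The efficacy outcome does not share this weakness to the same degree, because it is fixed at day 42, close to the treatment that differs.

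**Working it through.** **Plan's own figure.** The article gives a sample size for efficacy only: 162 evaluable and 196 recruited per arm, 80% power, two-sided 0.05. A two-proportion formula with 24% (the middle of the stated 22-26%) against 12% gives 160 per arm and 80.6% power at 162, so the formula used below agrees closely with the plan's figure. No AE rate or safety power is stated.

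**Shared doses.** Entry is at 16-26 weeks. I assume delivery at 37-40 weeks and 28-day spacing after day 63.
- Entry at 26 weeks, delivery at 37: (37 − 26) × 7 = 77 days, with SP on days 35 and 63, so 2 shared doses.
- Entry at 26 weeks, delivery at 40: 98 days, so 3 shared doses.
- Entry at 16 weeks, delivery at 37-40: 147-168 days, so 5 shared doses (days 35, 63, 91, 119, 147).

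**Assumed rates.** Medication-related event risk is 10% per SP dose, independent between doses. The share of the IPTp-SP+ arm taking DP is f = 24%; this uses PCR prevalence as a proxy, because RDT positivity is not stated. Risk after DP is 40% in one case and 20% in the other.

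**Formulas.**
- Early risk in IPTp-SP+: t = (1 − f) × 0.10 + f × r. With r = 0.40, t = 0.076 + 0.096 = 17.2%. With r = 0.20, t = 0.076 + 0.048 = 12.4%. Control is 10%.
- Risk to delivery after k shared doses: 1 − (1 − early risk) × 0.9^k. The difference between arms shrinks by the factor 0.9^k, which is 0.81 at k = 2 and 0.59 at k = 5.
- Power = Φ[(d − 1.96 × se0)/se1], with pooled standard error se0 and unpooled se1. Example, early window at 162 per arm: d = 0.072, se0 = √(0.136 × 0.864 × 2/162) = 0.0381, se1 = √((0.09 + 0.1424)/162) = 0.0379, so power = Φ(−0.07) = 47%.

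| Risk after DP | Shared doses counted | Control v IPTp-SP+ | Difference (points) | Power at 162 / 196 per arm |
|---|---|---|---|---|
| 40% | 0 (before day 35) | 10.0% v 17.2% | 7.2 | 47% / 55% |
| 40% | 2 | 27.1% v 32.9% | 5.8 | 21% / 24% |
| 40% | 5 | 46.9% v 51.1% | 4.3 | 12% / 13% |
| 20% | 0 (before day 35) | 10.0% v 12.4% | 2.4 | 10% / 11% |
| 20% | 2 | 27.1% v 29.0% | 1.9 | 6% / 6% |
| 20% | 5 | 46.9% v 48.3% | 1.4 | 4% / 5% |

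(Power counts rejection in the direction of the true effect only, so it can fall below 5%.)

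**Sensitivity.** If later SP doses carry only a 2% risk each, the shared later risk is 1 − 0.98^k, or 4.0% at 2 doses and 9.6% at 5. With 40% after DP, the risks to delivery become 13.6% v 20.5% and 18.6% v 25.2%. Power is then 38% / 45% and 29% / 34%, a much smaller loss from 47% / 55%.

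**The case against.** The strongest reply has four parts.

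- **The Cox analysis keeps timing.** The AE hazards are to be analysed with the methods set out for efficacy, which include Schoenfeld residuals, visual inspection and an extended Cox model when hazards are not proportional. An early excess that fades after day 35 is a non-proportional hazard. This stands: the Cox analysis is less exposed than the logistic one. It does not close the gap, because no cut point is fixed in advance and the remedy applies only if non-proportionality is found. The logistic comparison has no such remedy.
- **The long horizon is deliberate.** The objective names perinatal and infant events. The Discussion reports lower birth weight with DP than with SP. Sampling of "piperaquine plasma concentrations on days 0, 14, 28, 35, and 42" runs past the day-35 dose. Malaria during follow-up is treated with another antimalarial, so later drug exposure may also differ by arm. This stands, and it is why the 1-year outcome should not be demoted.
- **An early window does not rescue power.** Only RDT-positive women in one arm receive DP. A reader might infer from a 20% v 10% early difference by arm that the early window offers 71-79% power. At 24% taking DP, that difference would need a risk of (0.20 − 0.076)/0.24 = 52% in DP recipients. This also stands: dilution by RDT-negative women is separate and remains.
- **Splitting AE tables by period is routine analysis-plan detail.** This is partly fair. But the article itself states the primary safety analysis, and the only horizon it gives is 1 year.

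**Conclusion.** The point holds in a limited form. The primary safety outcome runs to 1 year, study drug differs by arm only at the first visit, and no early AE comparison is stated. A cumulative proportion is therefore pulled towards no difference for acute tolerability. The direction follows from the dosing schedule; the size does not. Under the assumed rates the loss is from 47-55% to 12-24% power when DP carries a 40% risk. It is less if later doses cause few events or if the same women react each time. If DP only doubles the risk, neither window detects much.

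A reader might infer that later events swamp the early contrast, or that everything after day 35 adds equally to both arms. The documents support neither: they give no AE rates, and piperaquine exposure and birth or infant effects can differ after day 35. Nor does the first 35 days' small share of calendar follow-up, 35/533 to 35/442 or 6.6-7.9%, measure the dilution, because no scheduled study drug follows delivery. This is an inexpensive improvement to the analysis, not a defect in the trial's conduct.

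**What to change.** Keep the 1-year maternal and infant safety outcome in Table 1 as stated. Add to the Statistical analysis section:

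1. A prespecified comparison by randomised arm of the proportion of women with at least one medication-related AE, and separately with at least one SAE, from the first dose until before the day-35 SP dose.
2. A supporting analysis by first drug received (DP or SP), labelled as non-randomised.
3. Events from day 35 to delivery, and infant events to 1 year, shown by arm as separate periods.
4. Day 35 named in advance as the cut point if the extended Cox model is used for AEs.

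The cost is a few sentences and a few more tables. Table 3 already schedules AE evaluation on days 0, 1-2, 14, 28 and 35. The article reports data collection as ongoing and keeps the statisticians masked until database lock, so the change can be fixed before unmasking. The downside is that late DP effects fall outside the early window, so the later periods must still be reported by arm. A null early result should also be reported with its confidence interval, because power there may be low.
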